Appendix. EQ-5D questionnaire …………………………………………………………22-23

**Background**

Traumatic brain injuries (TBI) are a major cause of morbidity and mortality leading to major long term consequences on both a personal and national level with an estimated 5.3 million Americans suffering from permanent TBI related disabilities [[1](#_ENREF_1)]. Due to improvements in emergency medical care, transportation and specialized trauma facilities, the number of people surviving TBI with impairment has significantly increased in recent years. The long term consequences of TBI are vast, affecting a large number of people with a substantial effect on the patients themselves, their families and society as a whole. These injuries also impart a significant economic burden on those involved, both personally and as a society. Approximately 80,000 – 90,000 individuals suffer from long term disabilities annually [[2](#_ENREF_2)], and the estimated costs including both direct medical care and indirect expenses. Lost earning potential, for example, were over 60 million dollars in 2001 in the US [[3](#_ENREF_3)].

The long term sequel of TBI may include impairment of the individuals physical, cognitive and psychosocial functioning. The neurological consequences are numerous and complex affecting various sites and functions. Sensory, motor and autonomic systems may all be affected and symptoms may include headaches, seizures, visual defects, movement disorders and sleep disorders. The cognitive consequences likewise are broad and varied. Amongst the symptoms most commonly noted are memory deficits and attention and concentration deficits. There may be impaired executive function, problem solving abilities and language difficulties as well as problems with planning, information processing, judgment and insight. While some of these symptoms may be apparent immediately after the injury, others may present days, weeks or months after the initial trauma [[1](#_ENREF_1),[4](#_ENREF_4)]. Among all patients suffering from TBI, mild TBI (mTBI) patients are usually under-diagnosed, and early intervention and rehabilitation is often neglected due to lack of contusions or hemorrhage detectable by anatomical imaging at the acute stage of the injury [[5](#_ENREF_5)]. About 70–90% of all treated brain injuries are mild, and the incidence of hospital administrated patients with mild traumatic brain injury is estimated to be 100–300/100,000 population. However, most of the cases of mild TBI are not treated at hospitals, and the true population-based rate is probably above 600/100,000 [[6](#_ENREF_6)].

Single photon emission CT (SPECT) scans have been found to be effective in evaluating post traumatic lesions in mild TBI patients and are useful for follow up of recovery. In a prospective study to evaluate the affectivity of SPECT scans in the diagnosis of patients with mTBI and its correlation with common clinical symptoms such as post concussion syndrome (PCS), post traumatic amnesia (PTA) and loss of consciousness (LOC), Gawda et al. [[7](#_ENREF_7)] found perfusion abnormalities in 63% of the patients. This as opposed to positive CT findings in only 34% of these patients. Hence, SPECT scan was found to be more sensitive than CT [[7](#_ENREF_7)].

Hyperbaric Oxygen Therapy (HBOT) has been in use since the 1930's when it was initially used for decompression sickness. Shortly thereafter physicians started using HBOT for a variety of other conditions. The use of HBOT for neurological indications started in the early 1960's with the work by Smith et al showing its protective effect in cerebral ischemia and that of Saltzman showing effectiveness in stroke patients [[8](#_ENREF_8)]. HBOT is the inhalation of 100% oxygen at pressures exceeding 1 atmosphere absolute (ATA) in order to enhance the amount of oxygen dissolved in the blood and body fluids, thereby allowing for increased oxygen delivery to the tissues. Under normobaric conditions, the amount of oxygen dissolved in the blood is only 0.3 ml/dl. At 1.5 ATA this amount increases 10 fold to 3.2 ml/dl. Using an animal model of brain injured mice Daugherty et al. [[9](#_ENREF_9)] found a 250% increase in the local brain tissue oxygen levels between 100% oxygen administered at 1 ATA (103 mmHg) as opposed to that given at 1.5 ATA (247 mmHg). This seems to suggest that dissolved O2 is more readily available to the brain tissue than hemoglobin bound oxygen [[10](#_ENREF_10)]. Additionally, work by several investigators seems to indicate that HBOT allows for more efficient use of baseline oxygen levels by injured brain tissue following treatments, which in turn leads to a positive persistent affect on this tissue [[10](#_ENREF_10)].

The mechanism by which HBOT is thought to improve the outcome of brain injury is multifaceted, The Neubauer and Walker theory postulates that HBOT improves cerebral metabolism by improving functioning of the dormant neurons and stimulating axonal growth [[11](#_ENREF_11)]. Zhang et al suggest that potential targets of oxygen therapy include prevention of apoptosis, inhibition of neuroinflammation and BBB damage [[12](#_ENREF_12)] . There is stimulation of angiogenesis and neovascularization, as well as direct effects on blood vessels in the brain, and maintenance of BBB integrity [[10](#_ENREF_10),[13](#_ENREF_13)]. Similarly, SPECT scans have demonstrated a positive effect on the cerebral blood flow (CBF) in the damaged brain following HBOT [[10](#_ENREF_10),[11](#_ENREF_11),[14](#_ENREF_14),[15](#_ENREF_15),[16](#_ENREF_16" \o "Neubauer, 1990 #402)].

There are well documented animal models of TBI and a growing body of literature using HBOT on these animal models verifying the above stated hypotheses and findings. Sun et al demonstrated improved penumbral oxygenation following HBO treatment in focal ischemia using an animal model by measuring both extrinsic and intrinsic markers of hypoxia [[17](#_ENREF_17)]. Harch et al used a rat model of TBI to evaluate HBOT effects on spatial learning and memory, as well as its affect on blood vessel density [[18](#_ENREF_18)]. HBOT also brings about improved neurocognitive functioning in patients suffering from chronic severe brain injury [[10](#_ENREF_10),[19](#_ENREF_19),[20](#_ENREF_20),[21](#_ENREF_21),[22](#_ENREF_22" \o "Shi, 2006 #410)]. However, none of these human trials were prospective, randomized clinical trials in TBI patients.

**Objectives**

The aim of the current study is to evaluate, for the first time in a prospective cross-over, randomized study, the effect of hyperbaric oxygen therapy (HBOT) on patients with chronic neurocognitive deficiency due to mild TBI.

- The primary endpoints of the study are to evaluate the effects of the HBOT on:
- Neurocognitive function (using Mindstreams neurocognitive battery)
- Brain metabolism (as visualized by SPECT)
- The secondary endpoints included quality of life evaluation.

The safety of the HBOT in this post TBI population will also be evaluated and any adverse event will be recorded.

**Study design**

A prospective, randomized, controlled, cross-over trial.

The study will be executed in the hyperbaric chamber and in the research and development unit of Assaf Harofeh Medical Center, Israel.

The brain SPECT evaluation will be executed in Nuclear Medicine institute in Assaf-Harofeh Medical Center, Israel.

**Inclusion criteria**

- An incident of mild traumatic brain injury 1-5 years prior to the inclusion in the study.
- All patients have to have complaints regarding persistent (stable not improving) neurocognitive deficiencies (memory, concentration, etc.) without noticeable improvement during the last month prior to their enrolment.
- Age 18 years or older.

**Exclusion criteria**

Patients will be excluded if they will have one of the following criteria:

- Dynamic neurologic improvement or worsening during the past month;
- Had been treated with HBOT for any other reason prior to their inclusion;
- Have any other indication for HBOT;
- Chest pathology incompatible with pressure changes;
- Inner ear disease;
- Patients suffering from claustrophobia;
- Inability to sign written informed consent;
- Smoking patients will not be allowed to smoke during the study and if they would not comply with this demand they will be excluded.

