***Study protocol***

After signing the informed consent, patients will be randomized in 1:1 manner into the treated or the control-cross group. After the randomization, patients will be invited for baseline evaluation that will include full review of their medical status and complete physical examination. All patients will present baseline anatomical scan (CT/MRI). After their inclusion, patients will be randomized to two groups: a treated group and a cross group. All patients will go through evaluation of their neurocognitive function using neurocognitive testing battery, quality of life using EQ-5D questionnaire and brain functional imaging (rCBF-SPECT scan). The patients in the treated group will be evaluated twice – at baseline and after 2 months of HBOT treatment. The patients of the cross group will be evaluated three times – at baseline, after a 2 month control period of no treatment and after a consequent 2 month period of HBOT treatment. We emphasize that the study will be a cross-over trial and patients in the cross group will receive HBOT treatment after their second evaluation and will go through a third neurological evaluation after the cross, when they will complete their HBOT.

The following HBOT treatment protocol will be practiced: The patients will go through 40 HBO treatments (each treatment session will be given on a separate day), distributed over two months (five days a week). Each session will be for 60 minutes in 100% oxygen atmosphere and at pressure of 1.5 ATA.

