***End-point evaluation***

**Neurocognitive evaluation**

The neurocognitive evaluation will be done at baseline and after 2 months for all patients. In the cross group a 3^rd^ evaluation will be performed after 4 month- after crossing and completing 2 months of HBOT treatment. Cognitive function will be assessed using the one-hour Mindstreams Computerized Cognitive Test Battery (Mindstreams; NeuroTrax Corp., NY). Detailed description of the tests can be found on Neurotrax website ([www.neurotrax.com](http://www.neurotrax.com)).

To minimize differences in age and education, each outcome parameter will be normalized and fit to an IQ-like scale (mean=100, S.D=15) according to patient's age and education. Normalized subsets of outcome parameters will be aggregated to produce four index scores relevant to mild TBI: **Memory, Attention, Executive function,** and **Information Processing Speed**.

Three different test versions exist in the Mindstreams testing battery to allow repeated administrations, test-retest reliability for those versions were evaluated and found high, with no significant learning effect [[23](#_ENREF_23),[24](#_ENREF_24)].

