### Primary Efficacy Analysis Set

The primary endpoint parameter: *improvement in neurocognitive tests scores* will be measured following HBOT treatment for post TBI patients suffering from chronic neurocognitive deficiencies.

The primary efficacy analysis evaluation will include all subjects who completed the HBOT treatment or the control period, had no major protocol violations, and for whom there is a valid *mindstreams score* at baseline and following 2 months of HBOT treatment.

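### Smoking during the study is written as an exclusion criterion, so randomised patients can be removed for later behaviour, with no provision to evaluate or analyse them

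*Protocol*

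**What the plan says.** The last bullet of the protocol's Exclusion criteria reads: "Smoking patients will not be allowed to smoke during the study and if they would not comply with this demand they will be excluded".

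On timing, the Study protocol section states: "After signing the informed consent, patients will be randomized in 1:1 manner into the treated or the control-cross group". The same section also places randomisation after inclusion. On either account it comes before the first session and before the control period.

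On follow-up, the same section says of one arm: "The patients in the treated group will be evaluated twice – at baseline and after 2 months of HBOT treatment". It says of the other: "The patients of the cross group will be evaluated three times – at baseline, after a 2 month control period of no treatment", followed by a further evaluation after HBOT. The Neurocognitive evaluation section dates that last visit: "In the cross group a 3^rd^ evaluation will be performed after 4 month- after crossing and completing 2 months of HBOT treatment". Both groups are planned to have 40 sessions on separate days, the cross group only after crossing.

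On analysis, the Primary Efficacy Analysis Set section says: "The primary efficacy analysis evaluation will include all subjects who completed the HBOT treatment or the control period, had no major protocol violations", and adds the condition "for whom there is a valid *mindstreams score* at baseline and following 2 months of HBOT treatment". The Randomization section states that patients will know their arm. The Safety Analysis Set keeps anyone who started treatment, but the protocol describes no efficacy set that keeps all randomised patients.

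**The concern.** An eligibility criterion should be decidable before a patient is randomised. This one is not: a smoker is admitted, allocated, and then excluded if they smoke afterwards. Randomisation makes the arms comparable only for the patients who were allocated. Once patients leave because of something they did after allocation, those who remain are a selected group.

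Patients who cannot stop smoking may differ from the others in cognition, cerebral perfusion or motivation, which bear on the two primary endpoints, Mindstreams and SPECT. If the rule bites at different rates in the two arms, the month-2 comparison is no longer between groups formed by chance alone. The single-cohort proportion of success in the Primary Efficacy Analysis would also be computed on a group selected by compliance.

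This is more than an analysis detail that a statistical analysis plan could settle later. If exclusion means that the month-2 tests are not done, no later analysis can bring those data back.

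**Working it through.** The protocol gives no figure for smoking or relapse, so there is no stated number to reproduce. The sample size of 31 plays no part in the conclusion. The check compares sections and counts planned contacts.

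**1. When the rule can act.** Randomisation follows consent and precedes both the treatment and the control period (Study protocol). The rule concerns smoking during the study. It therefore acts essentially on patients already randomised.

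**2. What follows exclusion.** The Exclusion criteria say only that the patient is excluded. The Neurocognitive evaluation section schedules the baseline and month-2 tests for every patient, but does not say whether that still covers someone excluded in between. The Primary Efficacy Analysis Set requires completion, no major violation and a valid post-HBOT score. An excluded smoker could fail any of the three.

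**3. Planned contacts at which smoking could be noticed** (Study protocol; Neurocognitive evaluation):

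| Period | Treated group | Cross group |
|---|---|---|
| Months 0–2 | 40 sessions + 2 evaluations = 42 | 0 sessions + 2 evaluations = 2 |
| Whole study | 40 + 2 = 42 over 2 months | 40 + 3 = 43 over 4 months |
| Per month, whole study | 42/2 = 21.0 | 43/4 = 10.75 |

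The gap lies in the randomised window. Over the whole study the totals are almost equal.

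**4. Time under the rule.** Up to month 2, both arms are under it for 2 months. To reach the post-HBOT score, the treated group must comply for 2 months and the cross group for 4.

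**5. What would set the size.** Let *f* be the fraction of an arm removed and *d* the mean difference in outcome between kept and removed patients in that arm. The mean of those kept differs from the full-arm mean by *f* × *d*. The month-2 contrast is then biased by

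*f*(treated) × *d*(treated) − *f*(cross) × *d*(cross),

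which is zero if both quantities are the same in both arms. The document supplies neither *f* nor *d*.

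The following is an illustration only, on assumed values. Let a proportion *s* of 20–40% be smokers, let 5–20% of them relapse per month (*h*), and let every relapse lead to exclusion. Then *f* after *m* months is *s* × [1 − (1 − *h*)^*m*].

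- Two months: 0.20 × (1 − 0.95²) = 0.020 up to 0.40 × (1 − 0.80²) = 0.144.
- Four months: 0.20 × (1 − 0.95⁴) = 0.037 up to 0.40 × (1 − 0.80⁴) = 0.236.

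For the post-HBOT analysis this means 2.0–14.4% removed from the treated group against 3.7–23.6% from the cross group. For the month-2 comparison, relapse itself is equal by construction, so any bias comes from detection. In the limiting case where every relapse is seen in the treated group and none in the cross group, with an assumed *d* of 0.5 SD, the bias runs from 0.020 × 0.5 = 0.01 SD to 0.144 × 0.5 = 0.07 SD. With equal detection and equal *d* it is zero.

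**The case against.** The strongest reply is that the protocol does not say assessments stop. It says excluded, and it plans the month-2 Mindstreams test for all patients. In the cross group, a lapse during the control period may first be noticed at the month-2 visit itself, when the outcome is being collected. This reply stands in part. A reader might infer that outcomes of excluded smokers are never collected or scored, and the text does not establish that. What it does establish is that no provision covers them after exclusion, and that the primary efficacy set could drop them even if they were tested.

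Four other inferences are tempting and do not hold:

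- *The cross group has fewer contacts.* This is true of its control period and of the monthly average, but not in total (43 against 42).
- *The longer period at risk distorts the month-2 comparison.* Both arms have 2 months by then. The extra 2 months affect only the cross group's post-HBOT score.
- *Untreated patients have less reason to comply.* They know their arm, but they are also promised HBOT after the second evaluation. The protocol does not support a direction.
- *One removed smoker can reverse the trial's result.* Against 0.02, the exact one-sided 95% lower limit is 0.027 for 3 of 31 and 0.012 for 2 of 31. The written success rule uses 0.12, where 8 of 31 passes (0.135) and 7 of 31 fails (0.111). A single response near a threshold decides any small binomial result. This says nothing about the effect of the smoking rule.

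It can also be said that the restriction to completers without major violations is the broader problem and that smoking is one route into it. That is fair. It means the analysis-set wording must change together with the bullet; it does not make the bullet harmless.

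**Conclusion.** The point holds in a limited form. A conduct rule sits among the entry criteria, it acts on randomised patients in an open-label trial, and nothing provides for evaluating or analysing them once excluded. In months 0–2 the opportunity to detect smoking is very uneven (42 planned contacts against 2), so removal may differ by arm. The 4-month compliance period adds a further imbalance for the post-HBOT analysis only.

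The size of the effect cannot be derived from the protocol. The illustrative figures rest wholly on assumed smoking rates, relapse rates and outcome differences, and on complete exclusion of those who relapse. They suggest a modest bias rather than one that decides the trial. Its direction is unknown. The conclusion itself rests only on the order of randomisation and the wording of the rule. It deserves a correction before data are lost, but it is not a fatal flaw.

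**What to change.** Four linked changes to the protocol:

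1. In the Exclusion criteria, limit the smoking bullet to what can be judged at entry, namely the patient's agreement not to smoke during the study.
2. Record smoking status at the existing evaluations, in the same way in both arms.
3. State in the Study protocol section that a randomised patient who smokes is still evaluated at month 2, and at month 4 in the cross group, and is analysed in the arm to which they were randomised.
4. Amend the Primary Efficacy Analysis Set so that smoking is not a major protocol violation that removes a patient from the randomised comparison. Keep the analysis without these patients as a sensitivity analysis. Without this step the set could still drop the same patients.

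The cost is a few amended sentences and one recorded item at visits already planned. The downside is that some patients who smoked remain in the analysis, which may dilute the effect slightly.

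Whether HBOT sessions continue for a patient who smokes is a clinical matter. The protocol says only that such patients are excluded, and no rule is proposed here.

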***Study protocol***

After signing the informed consent, patients will be randomized in 1:1 manner into the treated or the control-cross group. After the randomization, patients will be invited for baseline evaluation that will include full review of their medical status and complete physical examination. All patients will present baseline anatomical scan (CT/MRI). After their inclusion, patients will be randomized to two groups: a treated group and a cross group. All patients will go through evaluation of their neurocognitive function using neurocognitive testing battery, quality of life using EQ-5D questionnaire and brain functional imaging (rCBF-SPECT scan). The patients in the treated group will be evaluated twice – at baseline and after 2 months of HBOT treatment. The patients of the cross group will be evaluated three times – at baseline, after a 2 month control period of no treatment and after a consequent 2 month period of HBOT treatment. We emphasize that the study will be a cross-over trial and patients in the cross group will receive HBOT treatment after their second evaluation and will go through a third neurological evaluation after the cross, when they will complete their HBOT.

The following HBOT treatment protocol will be practiced: The patients will go through 40 HBO treatments (each treatment session will be given on a separate day), distributed over two months (five days a week). Each session will be for 60 minutes in 100% oxygen atmosphere and at pressure of 1.5 ATA.

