**Brain functional Imaging - SPECT imaging and Analysis**

Single photon emission computed tomography (SPECT) will be conducted before and after HBOT. Subjects will lay supine in a quiet dimly lit room for 20 min prior to injection of the radiopharmaceutical. Apart from administration of the injection by a physician, they will remain alone in the room during this period. Subjects will be asked to remain at rest for 10 min after the injection of the radiopharmaceutical to allow uptake of the radiopharmaceutical in the brain.

An injection of 925-1110 MBq (25-30 mCi) of technetium-99m ethyl cysteinate dimmer (Tc-99m-ECD) will be given into an arm vein through a previously placed intravenous cannula. SPECT imaging of the brain will be performed, at 40-60 min post injection, with the subject’s head supported by a headrest, using a dual detector gamma camera (ECAM or Symbia T, Siemens Medical Systems) equipped with high resolution collimators. Data will be acquired in the step-and-shoot mode, using a 360 degree circular orbit, with the detectors of the gamma camera as close as possible to the subject’s head. The camera used for imaging will be noted for each subject and the same camera will be used for the follow-up study. Data will be acquired using a 128׳128 image matrix in 3 degree steps of 20 seconds per step. Data will be reconstructed by iterative reconstruction with no filtering. The Chang method (*μ*=0.12/ cm) will be used for attenuation correction.

Intra subject visual analysis will be conducted using a process in which pre and post treatment studies are fused and normalized to pre-treatment whole brain activity.

Visual analysis will be carried out by two nuclear medicine physicians who compared the scans independently and grad them as either: 1=no change, 2=mild change and 3=significant change. Where, no change is assign when no visual difference is noted in the number or size of perfusion deficits, mild change is given when a reduced number of perfusion defects are noted or the size of the perfusion defects is reduced. Significant change should be attributed when a global perfusion increment is observed in addition to diminution of defect numbers or size. Differences in evaluation will be resolve after reviewing the images together. Scan visual interpretation will be carried out while blinded to any laboratory or clinical data.

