**Randomization**

Since the diversity of the patients included in the study, after signing the informed consent is expected to be high, no stratifies criteria will be used. Patients will be randomized in 1:1 fashion to either treatment or controlled-cross group.

There will be no placebo in the cross group during the control period. The only way to give “placebo” of HBOT, is to bring the patients to the hyperbaric chamber and to increase the environmental pressure in a way the patients will “feel the hyperbaric pressure” in their ears. However, Henry’s law states: “the amount of a given gas dissolved in a given type and volume of liquid is directly proportional to the pressure of that gas in equilibrium with that liquid”. Thus, hyperbaric environment significantly increases the dissolved oxygen pressure even if a person holding his breath [[29](#_ENREF_29)]. Moreover, the alternative of hosting the patients in the hyperbaric chamber without any pressure increase cannot serve as a real placebo since the patients will not feel the pressure. Accordingly, the only real “placebo” could be achieved by increasing the pressure and reducing the percentages of the oxygen but that holds significant safety consideration.

From the ethical point of view, it is deemed unethical to “treat” the patients (40 sessions in the hyperbaric chamber) while they actually know that it is a placebo. In order to somewhat compensate for this limitation, the control will be a cross group and after the 2^nd^ evaluation at the end of a control period they will be crossed to HBOT. The cross for treatment enables intra-group efficacy evaluation in both treatment and control group.

Since the patients will know they are not receiving HBOT during the control period they will not be blinded with regard to the treatment arm. Accordingly, the quality of life evaluations will not be blinded. However, the complete blindness evaluation can be assured in both of the primary end points of this study, The Mindstreams computerized evaluation and the brain SPECT evaluation done by the radiologist.

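### The Protocol gives two conflicting points of randomisation, neither clearly after the baseline tests, so unblinded patients could know their arm at baseline

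*Protocol*

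**What the plan says.** All the statements on sequence stand in the first paragraph of the Protocol's Study protocol section. In text order:

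- Consent leads straight to allocation: "After signing the informed consent, patients will be randomized in 1:1 manner into the treated or the control-cross group".
- The medical assessment comes next: "After the randomization, patients will be invited for baseline evaluation that will include full review of their medical status and complete physical examination".
- One sentence requires a baseline CT or MRI.
- Allocation is then stated a second time: "After their inclusion, patients will be randomized to two groups: a treated group and a cross group".
- Only after that are the outcome assessments listed: "All patients will go through evaluation of their neurocognitive function using neurocognitive testing battery", together with EQ-5D and SPECT.

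On blinding, the Randomization section says "There will be no placebo in the cross group during the control period" and, of the patients, that "they will not be blinded with regard to the treatment arm". It concedes that the quality-of-life assessment is not blinded, but holds that "the complete blindness evaluation can be assured in both of the primary end points of this study". For SPECT the imaging section adds: "Scan visual interpretation will be carried out while blinded to any laboratory or clinical data".

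Two passages on analysis bear on the point. Sample Size Considerations measures the improvement against the score before HBOT. Primary Efficacy Analysis Set admits only patients who completed their period, had no major violation and have valid Mindstreams scores at baseline and after two months of HBOT.

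**The concern.** In an open trial with an untreated control, the baseline measurement is protected only if it is taken before the patient learns the assignment. Here a patient could sit a one-hour cognitive battery already knowing whether treatment starts now or in two months. Effort on that test and answers on a health questionnaire can respond to such knowledge. A change score carries any error in its baseline in full, and later analysis cannot separate the two.

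The second issue is who remains in the comparison. If the medical review follows allocation, conditions on the exclusion list, such as chest pathology or inner ear disease, could be discovered in patients who already have an arm. Some patients may also withdraw once they learn that they must wait. Anyone lost between allocation and baseline has no baseline score and leaves the primary set. If that happens more often in one arm, randomisation no longer guarantees comparable groups.

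**Working it through.** The point concerns sequence and blinding and tests no planned figure. The check is therefore a reading of the passages, followed by an illustration of scale.

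**1. Do the two statements conflict?** The first puts allocation between consent and the medical review. The second puts it after inclusion, and it stands after the review and the CT/MRI. The patient is randomised once, so both cannot hold.

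**2. Does either reading put the outcome baselines before allocation?**
- First reading: the whole baseline evaluation follows allocation.
- Second reading: the medical review and scan may come first, which weakens the eligibility concern. The sentence listing Mindstreams, EQ-5D and SPECT still follows in the text. That sentence gives no time relative to allocation, so the text does not prove that these tests come later. Nothing places them earlier either.

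**3. Is the allocation withheld until baseline is complete?** No section says so.

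**4. Which endpoints are exposed?**
- Mindstreams: scored by computer, but the patient's effort is not blinded.
- EQ-5D: self-reported, and acknowledged as unblinded.
- SPECT: not effort-dependent and read without clinical data, so much less exposed.

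**5. How would an error pass through?** Percentage improvement = follow-up / baseline − 1. Take a true score of 100 (the mean of the normalised scale in Neurocognitive evaluation) with no real change. The shifts are assumptions.
- Baseline 2 points too low: 100/98 − 1 = 2.0%.
- Baseline 3 points too low: 100/97 − 1 = 3.1%.

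The Protocol's assumed test-retest effect is 2%.

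**6. What could this do to a comparison of the arms?** Assumptions, none from the Protocol: 31 patients per arm, SD of change 8 to 15 points, no true effect, one-sided 5% test of the difference in mean change. With a baseline depressed by d in the immediate-treatment arm, the false-positive rate is Φ(d / (SD × √(2/31)) − 1.645), where √(2/31) = 0.254. The standard error is 8 × 0.254 = 2.03 or 15 × 0.254 = 3.81.
- d = 2: Φ(0.984 − 1.645) = 25% (SD 8); Φ(0.525 − 1.645) = 13% (SD 15).
- d = 3: Φ(1.476 − 1.645) = 43% (SD 8); Φ(0.787 − 1.645) = 20% (SD 15).
- A 2-point depression in the waiting arm instead: Φ(−0.984 − 1.645) = 0.4% (SD 8); Φ(−0.525 − 1.645) = 1.5% (SD 15). The bias then runs against HBOT.

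**7. Loss before baseline.** Each patient lost is 1/31 = 3.2% of the stated sample. Sample Size Considerations does not say whether 31 is a total or a group size.

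**The case against.** The strongest reply is that the documents show less than a hostile reading would claim. Much of it stands.

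- **Eligibility may be settled first.** The Adverse Events section refers to a screening visit and Study Files to a screening and enrolment log. The second randomisation sentence also speaks of inclusion as already done. A reader might infer that exclusions would be found after allocation. The text supports only that they could be, because the screening visit is never placed in the sequence.
- **Knowledge at baseline is not stated.** The Randomization section says that patients know they are untreated during the control period. It does not say when they are told, or that the staff giving the tests know the arm. Staff knowledge is a possible inference only.
- **The waiting arm has a baseline.** A reader might infer that patients allocated to wait cannot enter the primary set for want of one. The Protocol schedules a baseline for all patients, so only those lost before it lack a score.
- **The planned rule is not a between-arm test.** Primary Efficacy Analysis declares success from a one-sided confidence limit on an observed proportion. Step 6 is therefore not the error rate of the planned rule. A wrong baseline would still alter each patient's improvement under that rule.
- **The completer set is a separate matter.** It would drop randomised patients whatever the order of visits.

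The reply does not remove the contradiction or the silence on withholding the allocation. The claim of blind evaluation covers how results are scored and read. It does not cover how hard an informed patient tries, or what that patient reports.

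**Conclusion.** The concern holds in limited form. The sequence contradicts itself, and neither version secures the Mindstreams and EQ-5D baselines against knowledge of the arm. Selective loss between allocation and baseline is possible and would pass into the primary set. The Protocol shows that bias is possible, not that it will occur, and it gives no basis for its direction or amount.

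The illustrations rest on assumed shifts of 2 to 3 points, 31 per arm and an SD of change of 8 to 15. They show only that a small disturbance would matter beside an assumed 2% test-retest effect. A reader might go further and set a 3-point shift against a 10-point target, calling it 30% of the effect sought. The documents do not support that: the Protocol states a target of 10%, which equals 10 points only for a baseline of 100, and the 3 points have no source. Nor should the concern be extended equally to SPECT.

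The sequence should be settled before enrolment, because a compromised baseline cannot be repaired in the analysis.

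**What to change.** In the Study protocol section, replace both randomisation sentences with one statement of order: informed consent; medical review and physical examination with CT/MRI; baseline Mindstreams, EQ-5D and SPECT; confirmation of eligibility; and only then generation and disclosure of the allocation. Deleting the earlier randomisation sentence alone would not be enough, since the outcome tests would still follow the remaining one. The screening visit named under Adverse Events should be given its place in the same sequence.

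The cost is amendment wording and a re-ordering of assessments already planned. A few patients will undergo baseline assessment, including a SPECT scan with its tracer injection, and then not be randomised. Doing the medical review first keeps that number down.

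The change does not resolve losses after baseline, or the cross group's second evaluation, which open-label patients necessarily take knowing that HBOT comes next.
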